## Abstract

**Background:**

Standard treatment for patients with disseminated germ cell tumors is combination chemotherapy with bleomycin, etoposide and cisplatin (BEP). This treatment is highly effective, but the majority of patients experience severe adverse effects during treatment and are at risk of developing considerable long-term morbidity, including second malignant neoplasms, cardiovascular disease, and pulmonary toxicity. One neglected side effect is the significant muscular fatigue mentioned by many patients with testicular cancer both during and after treatment. Very limited information exists concerning the patho-physiological effects of antineoplastic agents on skeletal muscle. The primary aim of this study is to investigate the effects of BEP-treatment on the skeletal musculature in testicular cancer patients, and to examine whether the expected treatment-induced muscular deterioration can be attenuated or even reversed by high intensity progressive resistance training (HIPRT).

**Design/Methods:**

The PROTRACT study is a randomized controlled trial in 30 testicular cancer patients undergoing three cycles of BEP chemotherapy. Participants will be randomized to either a 9-week HIPRT program (STR) initiated at the onset of treatment, or to standard care (UNT). 15 healthy matched control subjects (CON) will complete the same HIPRT program. All participants will take part in 3 assessment rounds (baseline, 9 wks, 21 wks) including muscle biopsies, maximum muscle strength tests, whole body DXA scan and blood samples. *Primary outcome*: mean fiber area and fiber type composition measured by histochemical analyses, satellite cells and levels of protein and mRNA expression of intracellular mediators of protein turnover. Secondary outcomes: maximum muscle strength and muscle power measured by maximum voluntary contraction and leg-extensor-power tests, body composition assessed by DXA scan, and systemic inflammation analyzed by circulating inflammatory markers, lipid and glucose metabolism in blood samples. Health related Quality of Life (QoL) will be assessed by validated questionnaires (EORTC QLQ-C30, SF-36).

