#### Primary outcome

Muscle biopsies will be collected from m. vastus lateralis using the Bergstrom-technique [7]. The muscle samples are immediately mounted with Tissue-Tek and frozen in isopentane cooled with liquid nitrogen, and stored at -80°C until further investigation. The post intervention biopsy will be obtained at 1 cm either distally or proximally (randomized) to the baseline biopsy.

*Mean fiber area *and *fiber type distribution *will be analyzed as described by Andersen & Aaagaard [5]. Serial sections (10 μm) of the muscle biopsy samples will be cut in a cryostat (-20°C), and routine ATPase histochemistry analysis will be performed after preincubation at pH 4.37, 4.60, and 10.30.

*Number and activation status of satellite cells *in muscle biopsies will be assessed by immunohistochemistry, as previously described by Mackey et al. [8]. The primary antibodies for Pax7, Type I myosin (A4.951), and laminin will be applied to the same section. In this approach, sites of Pax7 antigenicity are visible by light microscopy while fluorescence microscopy on the same section reveals which fibres are type I and type II. The same sections can be used to determine the number of myonuclei associated with type I and type II fibres. Active satellite cells can be distinguished from quiescent with the aid of double staining for satellite cells and Ki67, as described [9].

*Levels of Intracellular Signaling Molecules*: Gene expression of different signalling molecules involved in hypertrophy and atrophy, i.e. Insulin-like Growth Factor 1 (IGF-1) and Atrogin-1, will be measured by real-time Reverse Transcription Polymerase Chain Reaction (RT-PCR), as previously analyzed by our laboratory [10,11].

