### Sample size

Sample size is chosen to ensure significant muscular hypertrophy, evaluated by mean fiber area, in CON, among whom a 15% increase is estimated according to earlier studies.

N > (1,28*√(0.15*0.85))^2^/(0.15^2^) = 9,28. A minimum of 10 is required in each group, but due to clinical experience concerning possible drop out due to medical reasons 15 are included in each group.

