### Analytic Plan

1-way repeated measures Analysis Of Variance (RM-ANOVA) will be used to evaluate test-data within groups for assessments at baseline, 9 and 21 weeks. 2-way ANOVA (group × time) will be used to test the effect of HIPRT for TC patients (STR vs. UNT), and BEP-treatment for training response (STR vs. CON) respectively. The equivalent non-parametric tests will be used for mRNA expression and protein levels. Significance level of 0.05 is chosen.

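### At least four unranked measures share the primary label and each is tested in two group comparisons at 0.05, so the chance of some false primary finding is roughly 20–32%, not 5%

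*Protocol article*

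**What the plan says.** - **Abstract, Design/Methods.** One primary outcome label covers "mean fiber area and fiber type composition measured by histochemical analyses, satellite cells and levels of protein and mRNA expression of intracellular mediators".
- **Methods, Primary outcome.** The same families appear and are split further. Satellite cells become "Number and activation status of satellite cells". The signalling part names at least two genes: "Insulin-like Growth Factor 1 (IGF-1) and Atrogin-1, will be measured by real-time Reverse Transcription Polymerase Chain Reaction (RT-PCR". None is placed above another. Table 3 lists all endpoints by domain, with no primary or secondary rank.
- **Analytic Plan.** Two-way ANOVA (group by time) is used "to test the effect of HIPRT for TC patients (STR vs. UNT), and BEP-treatment for training response (STR vs. CON) respectively". In addition, a one-way repeated-measures ANOVA "will be used to evaluate test-data within groups for assessments at baseline, 9 and 21 weeks". The only statement on error control is "Significance level of 0.05 is chosen".
- **Sample size.** "Sample size is chosen to ensure significant muscular hypertrophy, evaluated by mean fiber area, in CON". This is the only place where one primary measure is treated differently from the rest, and it concerns the non-randomized control group.

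**The concern.** A primary outcome decides in advance which result will be read as the answer of the trial. Here at least four measures hold that position, each in two group comparisons, and no rule says how many must succeed or which one counts. An isolated difference in satellite cells or in one transcript could be reported as a positive primary result even if mean fiber area showed nothing. The two comparisons also carry different weight. STR versus UNT is randomized, whereas the Randomization section allocates CON without randomization, yet either could support a primary claim.

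**Working it through.** **The plan's own figure.** The article states no family-wise error rate. Its one calculation is the sample size: (1.28 × √(0.15 × 0.85))² / 0.15² = 1.6384 × 0.1275 / 0.0225 = 9.28. This reproduces and is rounded up to 10, with 15 enrolled per group. It concerns the expected 15% increase in CON and contains no term for STR versus UNT.

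**Inputs.**
- Primary measures: 4 (fiber area, fiber type, satellite cells, intracellular mediators), from the Abstract and the Primary outcome section.
- Between-group comparisons: 2, sharing the STR arm, from the Analytic Plan.
- Level: 0.05 per test, from the Analytic Plan. Sidedness is not stated; two-sided is assumed.
- Correlation between measures: not given. A common value from 0 to 0.9 is assumed.

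**Independent tests.** The chance of at least one false positive in k tests is 1 − 0.95^k.
- 4 measures × 2 comparisons, k = 8: 1 − 0.95⁸ = 0.337. The upper bound under any dependence is 8 × 0.05 = 0.40.
- 4 measures in one comparison, k = 4: 1 − 0.95⁴ = 0.185. The upper bound under any dependence is 0.20.

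**Shared arm and correlated measures.** The eight tests are not independent, because both comparisons use the same STR men and all measures come from the same biopsy. A simulation with three equal arms, equally correlated outcomes, normal z-tests, two-sided 0.05 and 200,000 runs per setting gave:

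| Correlation between measures | 4 measures, one comparison | 4 measures, both comparisons | 6 measures, both | 7 measures, both |
|---|---|---|---|---|
| 0 | 0.184 | 0.316 | 0.437 | 0.486 |
| 0.3 | 0.173 | 0.298 | 0.400 | 0.445 |
| 0.5 | 0.157 | 0.269 | 0.348 | 0.382 |
| 0.8 | 0.113 | 0.200 | 0.239 | 0.256 |
| 0.9 | 0.094 | 0.164 | 0.190 | 0.199 |

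Six measures result from splitting satellite cells into number and activation, and signalling into IGF-1 and Atrogin-1. Seven adds the protein levels that the Abstract names. Under full independence these would give 1 − 0.95¹² = 0.460 and 1 − 0.95¹⁴ = 0.512.

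**After the fix.** One measure and one comparison give 0.05. If all eight tests stayed primary, a Bonferroni level of 0.05 / 8 = 0.00625 would hold the rate at or below 0.05 (1 − 0.99375⁸ = 0.049 if independent).

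**The case against.** Several objections have force.

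- **One third is not a floor.** A reader might infer a false-positive chance of one in three or more. For the eight tests counted, 34% is the independence value. Once the shared STR arm is modelled, no setting in the four-measure column reaches one third. It is exceeded only by counting sub-measures or within-group tests. This stands.
- **Adding the within-group tests.** Three further tests per measure make 20, and 1 − 0.95²⁰ = 0.64. That is not a fair error rate for this trial. It treats as null the hypertrophy that the Sample size section expects in CON and the deterioration under treatment that the Abstract expects. These tests also reuse the same data. This stands, and the 64% should not be used.
- **Two separate questions.** STR versus UNT addresses training, and STR versus CON addresses BEP. Pooling them into one error family is a choice. Taken singly, each question has about 18.5% at most for independent or positively correlated outcomes. This stands as a smaller figure, but it is still well above 5%.
- **Small groups.** It is tempting to say that 10 to 15 men per group make chance findings likely. Small groups reduce power; they do not by themselves raise the type I error of a valid test.
- **An adjustment may sit elsewhere.** The article neither states nor excludes a multiplicity correction, and no analysis plan is shown. The absence of a correction is therefore not the point here. What remains is that this document itself fixes a several-part primary outcome without ranking. A later plan that chose one endpoint would depart from that published definition.

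**Conclusion.** The point holds in this form: at least four measures are primary without ranking, and each is tested in two group comparisons at one 0.05 level with no stated hierarchy. If no group truly differs, the chance of at least one false primary finding is about 34% for eight independent tests. It is roughly 20–32% with the shared STR arm and correlations from 0.8 down to 0, about 16% at a correlation of 0.9, and at most about 18.5% within one comparison for independent or positively correlated outcomes. It rises if the sub-measures are counted separately. The size rests on one test per measure and comparison, a common correlation that the article does not give, and no adjustment being made elsewhere. The structural defect does not depend on those assumptions.

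**What to change.** - Name mean fiber area as the single primary endpoint. It is already the sizing variable.
- Make STR versus UNT, baseline to 9 weeks, the primary contrast at two-sided 0.05. It is the randomized comparison, and it ends before UNT is offered HIPRT as rehabilitation.
- Keep STR versus CON on mean fiber area as a designated secondary, non-randomized comparison. The aim includes the effect of BEP on muscle, and this is the only between-group contrast that the Analytic Plan assigns to it.
- Make fiber type, satellite cells and signalling molecules secondary with Holm adjustment, or label them exploratory.
- Align the Abstract and the Primary outcome section.

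**Cost.** No assessment is lost and no data collection changes, but this is more than rewording. A result on satellite cells or mRNA alone, or on STR versus CON, could no longer be claimed as primary. The plan should also acknowledge that its sample size was derived for growth in CON and not for STR versus UNT, so the new primary contrast has no stated sample-size basis.

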**Discussion:**

This study investigates the muscular effects of antineoplastic agents in testicular cancer patients, and furthermore evaluates whether HIPRT has a positive influence on side effects related to chemotherapy. A more extensive knowledge of the interaction between cytotoxic-induced physiological impairment and exercise-induced improvement is imperative for the future development of optimal rehabilitation programs for cancer patients.

**Trial Registration:**

Current Controlled Trials ISRCTN32132990.

## Background

Testicular cancer (TC) is the most common form of cancer among young men in western countries [1], and remains the most curable solid tumor with a 10 year survival of 90 to 95% [2]. The standard treatment for patients with advanced germ cell cancer is 3 or 4 cycles of chemotherapy with cisplatin, etoposide and bleomycin (BEP) depending on prognostic factors. The treatment is highly effective, but the majority of patients experience severe adverse effects during treatment, and are at risk of developing considerable long-term morbidity, including second malignant neoplasms, cardiovascular disease, neurotoxicity, nephrotoxicity, pulmonary toxicity, hypogonadism, decreased fertility, and psychosocial problems [3]. In a study by Orre et al. the prevalence of chronic cancer related fatigue was 17.1% among TC patients compared to 9.7% in the general population. Regression analyses showed that poor quality of life (QoL), various psychosocial and somatic problems, and neuroticism were highly associated with presence of chronic cancer related fatigue [4].

Impaired muscular function and significant muscular fatigue are common complaints among TC patients undergoing chemotherapy. The cause of this muscular deconditioning is unknown, and knowledge regarding the effect of antineoplastic drugs on muscle function and morphology is very limited. There is also a lack of knowledge regarding whether TC patients will benefit from exercise training during chemotherapy.

The primary aim of the study is to investigate the effects of BEP-treatment on skeletal muscle, and to examine whether the treatment-induced muscular deterioration can be attenuated or even reversed by high intensity progressive resistance training (HIPRT) initiated on day 1 of the course of antineoplastic treatment. We have chosen a type of resistance exercise program that has proven to induce significant muscular hypertrophy in both healthy and diseased subjects [5]. Furthermore, the long term effect of an exercise rehabilitation program after the course of treatment will be investigated.

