#### Study arm 1: HIPRT for TC patients during and after BEP treatment (STR)

This group will conduct a 9 week HIPRT-program, initiated at day 1 of the treatment, and will be offered a 12 week rehabilitation-program after the course of chemotherapy.

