#### Study arm 2: Usual care for TC patients during BEP treatment and HIPRT as rehabilitation following treatment (UNT)

This group will receive standard care for the 9 week period during treatment, and will be offered a 12 week rehabilitation-program with HIPRT after termination of chemotherapy.

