We have chosen to investigate the effect of a structured HIPRT program initiated at day 1 of the treatment, to avoid a pre-intervention deterioration. Carrying out an exercise program during the course of a very toxic treatment obviously causes practical challenges due to side-effects like nausea or febrile neutropenia, which may lead to infections. Also TC patients are hospitalized for the first 5 days of each cycle where they receive treatment (chemotherapy and fluids) for 8 to 10 hours per day. This design however, allows us to investigate the direct effects of antineoplastic therapy on skeletal muscle. To minimize confounding factors it is important to eliminate the effect of the tumor itself as much as possible. For this purpose TC patients are optimal, as they have a very responsive tumor and most likely the disease has only minor influence after the first cycle. TC patients, however, may be affected by the presence of hypogonadism, which can significantly affect muscular adaptations to resistance exercise. Up to 50% of leydig cells are lost at unilateral orchiectomy [46], and subnormal levels of testosterone have been found in long term TC survivors [47,48]. In healthy subject it has been shown that suppression of testosterone attenuates the response to resistance training [49], however whether TC patients undergoing chemotherapy experience attenuated exercise response because of treatment induced hypogonadism is currently unknown.

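### The week 9 to 21 change cannot isolate a rehabilitation effect, because every arm has training in that period; and the wording on direct drug effects goes beyond what the UNT before-after change can show

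*Protocol article*

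**What the plan says.** All references are to the protocol article.

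- **Aims (Background).** The first part of the primary aim reads: "The primary aim of the study is to investigate the effects of BEP-treatment on skeletal muscle". The second part is whether training attenuates the deterioration. A further aim is added: "Furthermore, the long term effect of an exercise rehabilitation program after the course of treatment will be investigated".
- **Arms after week 9.** STR "will be offered a 12 week rehabilitation-program after the course of chemotherapy" (Study arm 1). UNT "will be offered a 12 week rehabilitation-program with HIPRT after termination of chemotherapy" (Study arm 2). CON trains for 21 weeks (Study arm 3).
- **Arms up to week 9.** STR and CON train; UNT has standard care. UNT is the only arm without training, and no untrained arm is off BEP.
- **Allocation (Randomization).** STR and UNT are randomized. CON is assigned to training without randomization, and is matched to the patients on age, BMI and training history (Healthy control subjects).
- **Tests (Analytic Plan).** A one-way repeated-measures ANOVA at baseline, 9 and 21 weeks "will be used to evaluate test-data within groups". Two-way group-by-time ANOVAs compare STR with UNT for the effect of training in patients, and STR with CON for the effect of BEP on training response.
- **Claim (Discussion).** The design "allows us to investigate the direct effects of antineoplastic therapy on skeletal muscle".

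**The concern.** An effect of rehabilitation is a difference between patients who have the program and comparable patients who do not. By design this trial has no such patients in weeks 9 to 21. Muscle may recover once BEP stops, whether or not the patient trains, and the within-arm change from week 9 to week 21 contains that recovery in full.

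A similar but narrower problem affects the drug question. How much untrained muscle deteriorates during BEP can be seen only as the change in UNT from baseline to week 9. That change is uncontrolled, yet the Discussion speaks of direct effects of therapy.

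At stake is the conclusion drawn from a significant within-arm p-value. If it were read as a rehabilitation effect or a direct drug effect, the design would not support that reading. The randomized comparison of STR with UNT at week 9 is not touched by this.

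**Working it through.** **1. Which comparisons exist**

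| Period | STR | UNT | CON (healthy) |
|---|---|---|---|
| Weeks 0 to 9 | BEP + training | BEP, standard care | training |
| Weeks 9 to 21 | program offered | program offered | training continues |

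- *Rehabilitation vs none, weeks 9 to 21:* no patient arm is in the second state. CON does not fill the gap, since it has no chemotherapy to recover from and is itself training. The Abstract can be read as giving CON only the 9-week program, whereas Study arm 3 gives 21 weeks. Neither reading supplies patients recovering without a program.
- *STR vs UNT at week 21:* randomized, but it compares early plus late training with late training only.
- *BEP vs no BEP in untrained muscle:* no comparator, so only the UNT before-after change is available.
- *BEP vs no BEP in trained muscle:* STR vs CON. It is concurrent, matched and planned, but not randomized, and it addresses training response rather than deterioration.

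**2. How often a within-arm test is significant if rehabilitation does nothing**

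The article gives no SD and no recovery rate, so the inputs are assumptions shown over a range:
- Fiber area falls 10% during BEP and returns to baseline by week 21 with no training effect. From week 9 the rise is 1.00/0.90 − 1 = 11.1%.
- The SD of the change is 10, 15 or 20%.
- The test is a paired t-test at two-sided 0.05. The article sets 0.05; two-sided is assumed. This stands in for the week 9 to 21 step of the planned three-timepoint ANOVA.
- n = 15 (enrolled per group) or n = 10 (the article's stated minimum). The stated minimum reproduces: (1.28 × √(0.15 × 0.85))² / 0.15² = 9.28, rounded up to 10. That calculation is sized on a change within CON and covers neither question here.

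With d = rise/SD, noncentrality = d√n and n − 1 degrees of freedom:

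| SD of change | d | n = 15 | n = 10 |
|---|---|---|---|
| 10% | 1.11 | 0.98 | 0.88 |
| 15% | 0.74 | 0.76 | 0.55 |
| 20% | 0.56 | 0.52 | 0.35 |

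If the recovery is scored instead as 10 points of baseline (d = 1.0 to 0.5), the ranges are 0.95 to 0.44 at n = 15 and 0.80 to 0.29 at n = 10. With no spontaneous change the figure is 0.05. A concurrent comparison with patients not offered the program would stay at 0.05 whatever the recovery.

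**3. Would an added arm be a realistic remedy?**

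For 80% power at two-sided 0.05 (normal approximation), n per arm = 2(1.96 + 0.842)²/d² = 15.7/d². This gives 63, 28 and 16 per arm for differences of 0.5, 0.75 and 1.0 SD. A third patient arm of 15 would fall short at all three, so restating the claim is the practical course.

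**The case against.** The rehabilitation half has no good answer: the arm descriptions leave no patient group without a program. The objections bear mainly on the BEP half.

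- **BEP does have a concurrent comparison.** This stands. A reader might infer that BEP is studied only through within-group changes, but the Analytic Plan includes STR vs CON under the same training progression. What remains is that this contrast is non-randomized and concerns training response, so it does not show deterioration of untrained muscle.
- **A direct effect is not a stated aim.** This also stands. The Background speaks of effects of BEP treatment; the word direct occurs only in the Discussion. There it may mean no more than measured during exposure, since the preceding text contrasts this trial with studies of patients who had finished treatment. The same paragraph mentions hospital stays, hypogonadism and the influence of the tumor. The word still invites a causal reading that those caveats contradict.
- **Some supposed confounders belong to the treatment.** Correct. Hospital days for infusion and treatment-induced hypogonadism are part of the total effect of BEP treatment. Tumor response, hypogonadism from orchiectomy and plain change over time are not, and the UNT change does not separate them from the drug.
- **Misreporting is presumed.** A reader might infer that the trial will report recovery as a rehabilitation effect. The article says only that the matter will be investigated and that data will be evaluated within groups, so this is not established. The point is that the aim, as worded, has no comparison that can answer it, and no later analysis plan can create one.
- **The figures are illustrative.** True. They rest on an assumed recovery and SD, and they do not size the BEP half.

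**Conclusion.** The concern holds in limited form. The rehabilitation aim cannot be answered as worded, because program and recovery are inseparable in weeks 9 to 21. Under the assumed full recovery from a 10% loss, a program with no effect would still give a significant within-arm change in 52 to 98% of trials at n = 15 and 35 to 88% at n = 10, for an SD of change from 20% down to 10%. These figures depend wholly on the assumptions; the conclusion about the design does not.

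On BEP, the finding is narrower: deterioration of untrained muscle rests on one uncontrolled before-after change, and the Discussion's wording on direct effects exceeds that. The documents do not support the stronger reading that BEP lacks any concurrent comparison. The planned STR vs UNT test of training is unaffected.

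**What to change.** 1. In the Background, restate the rehabilitation aim as the randomized STR vs UNT difference at week 21, that is, training during and after BEP against training after BEP only. The planned group-by-time ANOVA already compares these arms.
2. Report within-arm changes from week 9 to week 21, and the UNT change from baseline to week 9, as before-after estimates with 95% CIs. Label them *change during recovery/rehabilitation* and *change during BEP treatment*, not effects.
3. In the Analytic Plan, state that STR vs CON is a non-randomized comparison of training response.
4. In the Discussion, replace the phrase about direct effects with *changes during antineoplastic therapy*.

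No arm, patient or assessment is added. The downside is a more modest claim, about early versus delayed training rather than about rehabilitation itself. At 15 per arm the week-21 contrast will also be imprecise, so its confidence interval should be given with it.
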